## 7.3 SUBJECT WITHDRAWAL CRITERIA

### 7.3.1 Related to MVA.HIVconsrv vaccination

First MVA.HIVconsrv vaccination will only be administered if plasma viral load (pVL) is below the limit of detection in 2 consecutive determinations and CD4 cell count > 500 cells/ml at baseline. After RMD administration, low-level viral load detections (pVL<2,000 copies/ml) will be allowed only if suboptimal cART adherence is not suspected.

Any individual for who is being considered for discontinuation or postponement of vaccinations will be discussed with the trial team.

Participants might be discontinued or postponed -if clinical condition or laboratory abnormality is resolved within a maximum window of 10 days- from further vaccination for any of the following reasons:

- Ineligibility (either arising during the study or retrospective having been overlooked at screening).
- A disease, condition or an adverse event (including clinically significant abnormal laboratory values; see below) that develops, regardless of relationship to the study products, if, in the opinion of the principal investigator or designee, further vaccinations would jeopardize the safety of the patient.
- Hematology
  - Hemoglobin < 10.0 g/dl
  - Absolute Neutrophil Count (ANC)  $\leq 1000 /\text{mm}^3$  ( $\leq 1 \times 10^9 /\text{l}$ )
  - Absolute Lymphocyte Count (ALC)  $\leq 600 /\text{mm}^3$  ( $\leq 1 \times 10^9 /\text{l}$ )
  - Platelets  $\leq 50.000 /\text{mm}^3$ ,  $\geq 550,000 /\text{mm}^3$  ( $\leq 50 /\text{L}$ ,  $\geq 550 /\text{L}$ )
- Biochemistry

- Creatinine > 1.3 x ULN
  - AST > 2.5 x ULN
  - ALT > 2.5 x ULN
- Confirmed HIV-1 or HIV-2 re-infection.
- Pregnancy.
- Significant non-compliance with cART regimen or study requirements.
- Receipt of blood transfusion or blood products during this study.
- Participating in another clinical trial of an IMP.
- A serious adverse event judged to be possibly, probably or definitely related to vaccination.
- An adverse event which requires discontinuation of the study product or results in inability to continue to comply with study procedures.
- Loss to follow up.
- The safety of the volunteer would be jeopardized in the opinion of the investigator or sponsor.
- Investigator discretion.
- Significant protocol deviation.
- Disease progression, including virological failure (defined as a rebound in at least two consecutive determinations of pVL > 2,000 copies/ml after suppression), which requires discontinuation or modification of the study medication or results in inability to continue to comply with study procedures. Low-level pVL determinations just after vaccinations and/or during RMD administration will be allowed only if suboptimal cART adherence is not suspected.
- Consent withdrawn.

### 7.3.2 Related to romidepsin administration

Any individual for who is being considered for discontinuation or postponement of RMD administrations will be discussed with the trial team.

Participants might be discontinued or postponed -if clinical condition or laboratory abnormality is resolved within a maximum window of 7 days- from further romidepsin administration for any of the following reasons:

- Ineligibility (either arising during the study or retrospective having been overlooked at screening).
- A disease, condition or an adverse event (including clinically significant abnormal laboratory values; see below) that develops, regardless of relationship to the study products, if, in the opinion of the principal investigator or designee, further vaccinations would jeopardize the safety of the patient.
- Hematology
  - Hemoglobin < 10.0 g/dl
  - Absolute Neutrophil Count (ANC)  $\leq 1000 /\text{mm}^3$  ( $\leq 1 \times 10^9 /\text{l}$ )
  - Absolute Lymphocyte Count (ALC)  $\leq 600 /\text{mm}^3$  ( $\leq 1 \times 10^9 /\text{l}$ )
  - Platelets  $\leq 50.000 /\text{mm}^3$ ,  $\geq 550,000 /\text{mm}^3$  ( $\leq 50 /\text{L}$ ,  $\geq 550 /\text{l}$ )
- Biochemistry
  - Creatinine > 1.3 x ULN
  - AST > 2.5 x ULN
  - ALT > 2.5 x ULN
- Confirmed HIV-1 or HIV-2 re-infection.
- Pregnancy.
- Significant non-compliance with cART regimen or study requirements.
- Receipt of blood transfusion or blood products during this study.
- Participating in another clinical trial of an IMP.
- A serious adverse event judged to be possibly, probably or definitely related to romidepsin administration.
- An adverse event which requires discontinuation of the study product or results in inability to continue to comply with study procedures.
- Loss to follow up.
- The safety of the volunteer would be jeopardized in the opinion of the investigator or sponsor.
- Investigator discretion.

- Significant protocol deviation.
- Disease progression, including virological failure (defined as a rebound in at least two consecutive determinations of pVL > 2,000 copies/ml after suppression), which requires discontinuation or modification of the study medication or results in inability to continue to comply with study procedures. Low-level pVL determinations just after vaccinations and/or during RMD administration will be allowed only if suboptimal cART adherence is not suspected.
- Consent withdrawn.

### 7.3.3 Related to cART interruption

As persistent detectable viral replication may induce immune activation that could favor a faster viral rebound after cART cessation, cART interruption will only be indicated if plasma viral load (pVL) is below the limit of detection in 2 consecutive determinations, spaced at least 1 week, at MAP visit (MVA2+8w). In case that MVA.HIVconsv second booster immunization may induce repetitive detectable plasma HIV-1 RNA determination still present at MAP visit, cART interruption will be postponed until 2 consecutive determinations are achieved.

Any individual for who is being considered for postponement of cART interruption will be discussed with the trial team.

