## 7 SELECTION AND WITHDRAWAL OF SUBJECTS

### 7.1 INCLUSION CRITERIA

1. Subject included in ChAd-MVA.HIVconsv\_BCN01 study with complete follow-up and included in BCN01-RO extension study.
2. Willing and able to give written informed consent for participation in the study
3. Willing and able to keep a good adherence to their cART regimen for the duration of the intervention phase.
4. Optimal virological suppression for at least 3 years defined as maintained pVL below limit of detection (based on current available assays, 20 or 40 copies/ml) allowing for isolated blips (<200 cop/ml, non-consecutive, >10% total determinations).
5. Being on a non-boosted integrase-inhibitor based regimen (raltegravir or dolutegravir) for at least 4 weeks at screening visit.
6. No new AIDS-defining diagnosis or progression of HIV-related disease.
7. Haematological and biochemical laboratory parameters as follows:
  - a. Haemoglobin > 10g/dl
  - b. Platelets > 100.000/dl
  - c. ALT ≤ 2.5 x ULN
  - d. Creatinine ≤ 1.3 x ULN
8. Serology: negative for hepatitis B surface antigen; negative for hepatitis C antibodies OR confirmed clearance of HCV infection (spontaneous or following treatment).
9. Available for follow up for duration of study (baseline + at the most 54 weeks) and willing to comply with the protocol requirements
10. Age ≥18 years
11. CD4 T cell count ≥500 cells/mm^3

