#### **8.1.13 MVA2+4w – Four weeks post- MVA2 vaccination (13 weeks)**

Following procedures will be performed at both clinical sites (HGTIP and HC):

- Blood extraction including:
  - Viral load, biochemistry and hematological parameters and CD4 count.

- Plasma and PBMC storage following scheme detailed in attachment K
- cART adherence assessment (SERAD questionnaire)
- Clinical visit, adverse event register
- MVA2 +8w visit explanation and scheduling
- CRF data collection

In cases where pVL is detected >20 copies/mL at MVA2 + 4w, an extra visit will be scheduled at MVA2 + 6w including the following procedures:

- Blood extraction including:
  - Viral load, biochemistry, hematological parameters and CD4 count.
  - Plasma and PBMC storage.
- cART adherence assessment (SERAD questionnaire)
- Clinical visit, adverse event register
- MVA2 +8w visit explanation and scheduling
- CRF data collection

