#### **8.1.14 MAP – Monitored antiretroviral pause and MVA2+8w – Eight weeks post MVA2 vaccination (17 weeks)**

Following procedures will be performed at both clinical sites (HGTIP and HC):

- Blood extraction including:
  - Viral load, biochemistry and hematological parameters.
  - Plasma and PBMC storage following scheme detailed in attachment K
- cART adherence assessment (SERAD questionnaire)
- Clinical visit, adverse event register
- Review acceptability for cART interruption after interim analyses (which will be performed at week 13 and be provided by investigational team in advance and recorded in 'Indication for MAP phase' form, attachment X)
- Review acceptability for cART interruption regarding plasma viral load suppression (pVL below the limit of detection in 2 consecutive determinations, spaced at least 1 week, and recorded in 'Indication for MAP phase' form, attachment X)
- Phase 2 study explanation including: cART interruption, site, weekly clinical visit, qualitative plasma viral load monitoring, criteria for cART resumption.
- CRF data collection

Once analytical results are available, cART interruption will be confirmed telephonically by study physician and first visit in BCN-Checkpoint will be scheduled.

In cases where pVL is not undetectable for 2 consecutive determinations, MAP will be postponed and extra visits will be scheduled (every week if pVL is 20-500 copies/mL, every two weeks if pVL is >500 copies/mL) including the following procedures until acceptability criteria for cART interruption are met.

- Blood extraction including:
  - Viral load, biochemistry and hematological parameters.
  - Plasma and PBMC storage.
- cART adherence assessment (SERAD questionnaire)
- Clinical visit, adverse event register

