#### 8.1.16 cART resumption visit (7-10 days after first Qual pVL positive)

pVL-pos+7d visit will be performed at BCN-Checkpoint.

Following procedures will be performed:

- Reporting of symptoms suggestive of acute retroviral syndrome (including its severity grade)
- Discussion on treatment resumption based on following considerations (attachment M):
  - o If viral load is >2,000 copies/mL in visits pVL-pos and pVL-pos+3d, and/or clinical symptoms, laboratory abnormalities or significant drops in CD4 T cell counts (>50% &/or <500) have been detected, patients will be recommended to re-start cART immediately.
  - o If viral load is <2,000 copies/mL in visits pVL-pos and >2,000 copies/mL in visit pVL-pos+3d, and/or clinical symptoms, laboratory abnormalities or

significant drops in CD4 T cell counts (>50% &/or <500) have been detected, patients will be recommended to re-start cART immediately.

- If viral load is > or <2,000 copies/mL in visits pVL-pos and <2,000 copies/mL in visit pVL-pos+3d, and NO clinical symptoms, laboratory abnormalities or significant drops in CD4 T cell counts have been detected cART will not be resumed.
- cART prescription\* at the Pharmacy Unit
- Follow-up explanation and cART+4w visit scheduling (or a follow-up MAP visit at BCN-Checkpoint if cART is not resumed)
- CRF data collection

\*cART regimen will at the discretion of the study physician, according to clinical criteria (no changes on patient's previous cART regimen are envisioned as no emergence of drug resistances is expected)

Overall, time since 1st positive HIV-1 Qualitative detection to cART resumption is aimed to be <10 days to avoid fast viral reservoir replenishment.

[figure not shown]

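### The body text lets cART be stopped without a CD4 check, yet advises restart on a CD4 fall with no named reference count and two different floors

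*Protocol*

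**What the plan says.** **Stopping cART.** Section 7.3.3 sets a virological condition: "cART interruption will only be indicated if plasma viral load (pVL) is below the limit of detection in 2 consecutive determinations". Sections 7.3.4 and 10.2 add that stopping is discouraged if the booster is no longer immunogenic, and 10.2 also covers persistent viremia. The week-17 visit in 8.1.14 has two acceptability reviews. One uses the week-13 interim immunogenicity result; the other reads "Review acceptability for cART interruption regarding plasma viral load suppression". None of these places mentions CD4.

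**Tests around the stop.** The blood draw at week 17, and at each postponement visit, is listed as "Viral load, biochemistry and hematological parameters". Four weeks earlier, 8.1.13 lists "Viral load, biochemistry and hematological parameters and CD4 count". Section 8.4.2 places CD4 under immunology, so the haematology panel does not include it.

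**Restarting cART.** In 8.1.16, if "significant drops in CD4 T cell counts (>50% &/or <500) have been detected, patients will be recommended to re-start cART immediately". The branch that keeps the participant off therapy requires viral load below 2,000 at the +3d visit "and NO clinical symptoms, laboratory abnormalities or significant drops in CD4 T cell counts have been detected cART will not be resumed". Section 8.1.15 also counts a CD4 drop among the considerations for resumption at MAP weeks 2, 4, 8 and 12 and monthly afterwards, with no figure attached. Secondary endpoint 3.5 (5.3.2) counts restarts and gives the CD4 floor as 450 cells/mm³.

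**Earlier CD4 conditions.** Inclusion requires "CD4 T cell count ≥500" (7.1). The first vaccination requires viral load "below the limit of detection in 2 consecutive determinations and CD4 cell count > 500 cells/ml at baseline" (7.3.1; I read the unit as cells/mm³, as in 7.1).

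**The concern.** The rule for leaving therapy and the rule for returning to it do not use the same information. CD4 can bring a participant back onto cART, but in the visible text it plays no part in taking the participant off. Between the baseline CD4 condition and the pause come three romidepsin infusions and a second vaccination.

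Two things follow. A participant whose count is already below the restart floor can begin the pause. And because no pre-pause count is named as reference, two physicians can measure the same fall from different starting points and give opposite advice. At stake are the safety logic of the pause and, through endpoint 3.5, how restarts are classified.

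**Working it through.** The protocol gives no figure to reproduce here. The check sets the rules side by side, works out the age of the last count, and tests how much the missing reference matters.

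**1. Use of CD4, in time order (body text)**

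| Step | CD4 condition | CD4 count listed |
|---|---|---|
| Inclusion (7.1) | at least 500 | – |
| First vaccination (7.3.1) | above 500 | – |
| Weeks 3 to 13 | none | 8: RMD1, RMD1+3d, RMD2, RMD2+3d, RMD3, RMD3+3d, RMD3+1w, MVA2+4w |
| Week 15, only if week-13 viral load was above 20 | none | yes |
| Stop at week 17, and postponement visits (8.1.14) | none | no |
| Weeks 19, 21, 25, 29 (8.1.15) | a drop is considered, no figure | yes |
| Restart visit (8.1.16) | >50% and/or <500 | from the pVL-positive and +3d draws |
| Endpoint 3.5 (5.3.2) | >50%, <450 | – |

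**2. Age of the last routine count**

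- On-time stop: 17 − 13 = 4 weeks.
- First scheduled count on the pause: 19 − 13 = 6 weeks after the last one, or 18 − 13 = 5 if the week-18 qualitative test is positive.
- MVA2+12w is week 9 + 12 = 21. Stopping later than that makes the count more than 21 − 13 = 8 weeks old, or more than 21 − 15 = 6 if the week-15 visit took place. At that point 8.1.14 repeats the ELISPOT but lists no CD4 count.

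A change between the last count on cART and the stop therefore cannot be separated from a change on the pause.

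**3. Two readings of 8.1.16**

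- *Reading A: below 500 is an absolute level.* Someone already below 500 starts the pause while meeting a restart reason. The 50% limb adds something only if half the reference exceeds 500, that is, if the reference exceeds 1,000.
- *Reading B: below 500 means a drop to that level.* The rule then cannot be applied without a reference count, and none is named.

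Example with assumed counts, for an on-pause count of 520:

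- from a baseline of 1,100: (1,100 − 520)/1,100 = 52.7%, restart;
- from a week-13 count of 900: (900 − 520)/900 = 42.2%, no restart.

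**4. Two floors.** A whole-number count from 450 to 499 is below the floor in 8.1.16 but not below the one in endpoint 3.5.

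**5. What a hard gate at 500 would do.** Assume log-normal within-person variation and independent readings. For true count m and coefficient of variation CV, the chance that one reading is below 500 is p = Φ((ln 500 − ln m)/s), with s = √ln(1 + CV²). Two readings are both below with probability p².

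| True CD4 | Result | CV 10% | CV 15% | CV 20% |
|---|---|---|---|---|
| 550 | held back on one count (p) | 17.0% | 26.1% | 31.5% |
| 550 | held back after a repeat (p²) | 2.9% | 6.8% | 9.9% |
| 480 | passes with a repeat (1 − p²) | 57% | 63% | 66% |
| 400 | passes with a repeat (1 − p²) | 2.5% | 13.0% | 24.3% |

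A single-count gate would often hold back people who are truly above 500. Even with a repeat, the check mainly picks out clear cases. The CVs are assumptions; the protocol gives none.

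**The case against.** **Unseen material.** Section 8.1 sends the reader to attachment J for the procedures at each visit. Attachment X records the stop decision, and M and AB are the decision charts. None is shown, nor are the figures in 8.1.14 and 8.1.16. The visit lists in the body are also incomplete: 8.1.1 does not name CD4 and 8.1.2 lists no blood draw, although 7.1 and 7.3.1 need a CD4 count. This stands. A reader might infer that no CD4 count is taken at week 17; the documents do not support that. They support only that the visible text neither lists one nor ties one to the stop.

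**A dropped half-rule.** A reader might infer that 7.3.3 copied the viral-load half of 7.3.1 and lost the CD4 half. The text does not bear this out. The CD4 condition in 7.3.1 applies to the first vaccination only, and 7.3.3 gives its own virological reason: ongoing replication may activate the immune system and speed rebound.

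**A recent count exists.** The week-13 count comes from the same visit as the interim analysis and largely serves an on-time pause. This stands, but the text does not name it as the reference, and it ages when the pause is postponed.

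**Small consequence.** In 8.1.16, CD4 decides the outcome only after a positive qualitative test, with viral load below 2,000 at +3d and no symptoms or laboratory abnormality. Reading A is also strained, since a stable 480 is not a drop, and its error is towards therapy. The section guides a discussion, and the trial team and the withdrawal clause in 7.3.4 leave room for judgement. All this limits the size of the point. It does not supply a reference count, and 8.1.15 lets a CD4 drop weigh on resumption outside that narrow branch.

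**Conclusion.** The point holds for the visible body text. The conditions for stopping cART contain no CD4 check, no CD4 count is listed at the stop or postponement draws, the restart rule in 8.1.16 has no reference count, and the floor is 500 there but 450 in endpoint 3.5. It weighs most when the pause is postponed and the last routine count may be more than 8 weeks old; for an on-time pause it is largely met by naming the week-13 count.

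The number of participants affected cannot be derived: the protocol gives no CD4 distribution and enrols at most 24. The 1,100/900 example and the CVs are assumptions. A reader might conclude that a hard eligibility gate at 500 is needed. The documents do not require one, and with at most 24 participants and no replacement (7.3.7) it would be a real trade-off. This is a change the sponsor should make for safety and consistency; it does not show that any endpoint is biased.

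**What to change.** 1. In 8.1.14, add a CD4 count to the week-17 and postponement draws. If no new assay is wanted, let the week-13 count serve for an on-time pause.
2. In 8.1.16, name the latest pre-pause CD4 count as the reference for the drop, and record it on the form in attachment X.
3. Use one restart floor in 8.1.16 and endpoint 3.5.
4. In 7.3.3 and 10.2, state that if the latest pre-pause count is below that floor, it is repeated and the trial team reviews the case before cART is stopped. Do not apply a hard single-count gate.
5. If attachment J, M, X, AB or a figure already carries a CD4 line, align the body text with it.

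Cost: one assay per participant on blood already taken (one more at each postponement draw), a few lines of text, and an occasional short delay. With a floor of 500 and a true count of 550, the assumptions above give a first reading that needs a repeat in 17.0% to 31.5% of cases and two low readings in 2.9% to 9.9%. Under this fix, two low readings lead to review, not automatic exclusion from the pause.

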### 7.3.4 Early subject withdrawal

The patients will complete the clinical study before the stipulated time in the following circumstances:

- Concurrent process or illness which in the opinion of the investigator requires the withdrawal of the patient.
- Protocol deviation which in the opinion of the sponsor requires the withdrawal of the patient.
- The patient does not wish to continue in the study.
- Other

On the other side and in order to minimize risks of the treatment interruption intervention, an early interim and futility analyses is planned before the MAP phase for each individual. Treatment interruption would be discouraged if boosting MVA.HIVconsv is shown to be no longer immunogenic after romidepsin administration –defined as no net increase of HIVconsv-specific IFN $\gamma$  response compared to pre-vaccination levels with MVA.HIVconsv at BCN02-Romi baseline visit, due to RMD toxicity on CTL functional

activity for instance, as an improved viral control would not be foreseen. These results are considered valid for up to 12 weeks from the second vaccination. As vaccine induced T-cells may decrease in the following weeks and available data on expected kinetics of immune response is limited, in the event that the cART interruption is postponed more than MVA2 + 12w, the futility analyses should be repeated and results will be discussed among the investigators

In such situation, trial results would be focused on the viral reservoir and immunogenicity endpoints only until better correlates of control would be available to predict clinically relevant outcomes on which one could recommend treatment interruptions in a safer manner.

### 7.3.5 Medical approach to withdrawal

In all cases, 'end of study form' is to be filled. Detailed information will be given about the date and reasons of the discontinuation to the sponsor. The investigator will facilitate the necessary medical support to the patient.

### 7.3.6 Follow-up after early withdrawal

That is, as a general rule, all patients who discontinue treatment prematurely will undergo a clinical examination and all tests specified in the visit.

In case early withdrawal happens while patient is receiving IMP, a follow-up of 28 days after the last IMP dose will be performed for AEs collection.

### 7.3.7 Replacement of patients

Replacement of patients will not be possible, since the number of candidates is limited to the participants of the BCN01-RO

## 7.4 PRE-RANDOMIZATION / PRE-BASELINE LOSSES

Data from patients that do not meet the selection criteria after completing the screening visit will not be considered for the study, but the reason for not meeting selection criteria will be recorded in the screening log form in an anonymised manner.

## 8 TRIAL CONDUCTION AND RESPONSE EVALUATION

### 8.1 TRIAL DEVELOPMENT

Participants included in the extension phase of the BCN01 trial (BCN01-RO) will be contacted by principal investigator or collaborators and participation into the BCN02-Romi will be offered. A meeting with the investigator will be scheduled, if they wish. Participants will be provided with information on the MVA.HIVconsv vaccine and romidepsin and the study protocol and will be offered the Participant Information Sheet. Patients will have the opportunity to ask questions and to arrange an appointment for a screening visit if they wish. In the scheduling of screening visits it will be ensured that potential participants have adequate time to decide whether to participate.

Screening visit will be scheduled.

Detailed Schedule of Procedures in every visit is found in attachment J.

